## Abstract

**Introduction:**

Methamphetamine use disorder is a significant public health concern. No pharmacological treatment options currently exist for methamphetamine use disorder, and psychotherapy is only moderately effective. Preliminary evidence suggests that ketamine-assisted psychotherapy produces sustained improvements in substance use and mental health symptomatology. In addition to direct antidepressant properties, ketamine is hypothesised to increase synaptogenesis and facilitate neuroplasticity, in turn prolonging and enhancing the effects of psychotherapy. Given the withdrawal-associated dysphoria and neurocognitive impairments characterising methamphetamine use disorder, ketamine-assisted psychotherapy may improve the efficacy of psychotherapy alone by addressing these features and facilitating therapeutic engagement. This pilot study aims to investigate the safety and feasibility (time taken to recruit sample, proportion of ineligible participants at pre-screening and screening, number of participants who complete four sessions of psychotherapy, retention rate over full duration of study, acceptability of the intervention) of subanaesthetic ketamine in combination with psychotherapy (cognitive behavioural therapy) for adults with methamphetamine use disorder. Changes in methamphetamine use, cravings and withdrawal, quality of life, and treatment satisfaction will also be explored.

**Methods and analysis:**

This is an open-label, single-arm clinical trial. 20 adults meeting DSM-5-TR criteria for methamphetamine use disorder who are seeking to reduce or cease methamphetamine use will be enrolled in the study through a single-site specialist outpatient stimulant treatment service in inner Sydney (St Vincent’s Hospital, Sydney). A 4-week course with three subcutaneous ketamine doses (0.75 mg/kg to 0.9 mg/kg, titrated according to tolerability) at weekly intervals and four sessions of cognitive behavioural therapy (one at treatment initiation and three within 24–48 hours following each ketamine administration session) will be delivered. Safety and feasibility will be assessed over an 8-week period. Secondary outcomes (changes in methamphetamine use, cravings, withdrawal, quality of life and treatment satisfaction) will be assessed over a 24-week period.

**Ethics and dissemination:**

This study has been approved by the St Vincent’s Hospital Human Research Ethics Committee, reference 2023/ETH00530. Study findings will be disseminated through articles in scientific, peer-reviewed journals, and at national and international conferences.

**Trial registration number:**

ANZCTR: ACTRN12624000895583.

**Protocol version:**

The trial protocol (Version 4.0) was approved on 24 June 2024.

STRENGTHS AND LIMITATIONS OF THIS STUDYThe KAPPA pilot study is the first to examine the safety and feasibility of ketamine-assisted psychotherapy for methamphetamine use disorder.Structured clinical intervention of standardised manual-based cognitive behavioural therapy alongside a rigorous low-cost subcutaneous racemic ketamine dosing protocol allows for ready reproducibility.Moving beyond abstinence, the study tests the feasibility of measuring validated secondary outcomes that align with harm-reduction and person-centred approaches, including reduction in methamphetamine use and improved quality of life.A strength of the study is the use of structured clinical interviews to screen and characterise the sample.There is a risk of high attrition rates over the course of the study.

## Introduction

### Background and rationale

 Methamphetamine is the most widely consumed synthetic stimulant drug worldwide,^1^ representing a significant public health concern. Frequent methamphetamine use is associated with a variety of health problems including mental health conditions, insomnia, cardiovascular conditions, cognitive deficits and a risk of drug-induced psychosis.^2 3^ Methamphetamine use disorder (MAUD) often involves increasing tolerance to methamphetamine and continued use to avoid the withdrawal symptoms that follow abrupt cessation.^4^ In 2020–2021 in Australia, methamphetamine accounted for 8.2% of all drug-related hospitalisations and is associated with an increasing rate of drug-related deaths (almost four times higher in 2022 compared with 2000),^5^ highlighting a need for a greater range of effective treatments for this group.

No regulatory-approved pharmacological treatment options currently exist for MAUD. Evidence to date for candidate therapeutic agents from a variety of drug classes is promising but limited.^6^,^11^ The current standard of care therefore relies on psychosocial interventions, primarily cognitive behavioural therapy-based approaches,^12^ which show modest effectiveness.^13^ Relapse to methamphetamine use rates is high, with only one-quarter of individuals remaining abstinent after 1 year following residential rehabilitation.^14^ Further, treatment outcomes differ depending on levels of use, with poorer outcomes observed in people who use methamphetamine frequently compared with those who use less frequently.^15^ Limited efficacy may be due in part to psychosocial interventions not sufficiently addressing cravings and the presence of negative affect during withdrawal, leading to relapse,^16^ or common neurocognitive difficulties observed in MAUD including executive dysfunction, poor working memory, impulsivity and decision-making difficulties.^17^ Supporting psychological interventions with adjuvant pharmacotherapy may overcome some of these challenges, an approach which is beginning to show promise with other substance use disorders.^18^

Combined treatment approaches using ketamine and different forms of psychotherapy (referred to as ketamine-assisted psychotherapy; KAP) have shown sustained improvements in treatment outcomes for a variety of mental health and substance use disorders.^19 20^ Ketamine is a well-characterised dissociative anaesthetic, acting primarily through antagonism of the glutamatergic n-methyl-d-aspartate (NMDA) receptor. Racemic ketamine is used therapeutically as an anaesthetic agent and analgesic (administered parenterally) and in its s-enantiomer form as esketamine, administered intranasally for treatment-resistant depression. Glutamatergic dysregulation has been implicated in depression.^21^,^24^ Subanaesthetic doses of ketamine induce rapid reversal of depression symptoms that can be sustained for up to 7 days after one infusion.^23 25^ The antidepressant properties of ketamine are of particular interest for amphetamine use disorders given findings that chronic amphetamine administration results in depletion of dopamine receptors and dopamine release, leading to a negative affective state during withdrawal,^16^ and increasing the risk of relapse.^26^ While there is significant heterogeneity in how ketamine has been administered in clinical studies to date (eg, intravenous infusion vs subcutaneous injection, dosage, course of treatment), preliminary data suggest that subanaesthetic doses of ketamine may have efficacy for treatment of substance use disorders. Ketamine monotherapy for cocaine, heroin and alcohol use disorder has produced short-lived improvements in self-administration and abstinence compared with active placebo.^20 27 28^ While ketamine provides a unique, rapid onset of antidepressant action for chronic mental health conditions including substance use disorders, its therapeutic effect is temporally limited. Symptom reductions are frequently transient (typically lasting 4–7 days), with repeated administrations required to maintain positive effects.^29^,^31^

In KAP approaches, it is hypothesised that ketamine may prolong and enhance the effect of psychotherapy by increasing synaptogenesis and promoting neural pathways which facilitate neuroplasticity.^19 20^ Ketamine-enhanced neuroplasticity is thought to facilitate emotional learning, evoke emotionally arousing phenomenological experiences, reduce defensiveness and enhance treatment adherence and engagement.^19^ While no studies to date have examined KAP for MAUD specifically, promising findings for other substance use disorders have been reported. A small randomised controlled trial (RCT; n=55) of ketamine-assisted (0.5 mg/kg single intravenous infusion) mindfulness-based relapse prevention therapy for cocaine dependence showed 48.2% abstinence compared with 10.7% in the active control group (midazolam+mindfulness-based relapse prevention therapy), with the odds of end-of-study abstinence in the ketamine group being six times that in the midazolam group (OR=5.7, ᵡ^2^=5.34, df=1, p=0.02). Further, those in the ketamine group were 53% less likely to relapse or discontinue treatment compared with controls over the 5-week study period.^32^ An RCT (n=40) examining ketamine-assisted (0.71 mg/kg single intravenous infusion) motivational enhancement therapy for alcohol use disorder reported a lower proportion of participants in the ketamine group using alcohol (8/17, 47.1%) compared with controls (13/22; 59.1%) across the 21 days following drug administration.^33^ Sustained effects have been reported in alcohol use disorder, whereby those receiving ketamine-assisted (three 0.8 mg/kg intravenous infusions once weekly) mindfulness-based relapse prevention therapy had more days abstinent over 6 months compared with three other groups (ketamine+psychoeducation; placebo+mindfulness-based relapse prevention therapy; placebo+psychoeducation) (mean difference=10.1, 95% CI=1.1, 19.0).^34^ Longer-term effects in other substance use disorders have also been reported. An RCT (n=70) in people with heroin dependence using both a high (2.0 mg/kg) and low (0.2 mg/kg) intramuscular ketamine dose and existential-oriented psychotherapy reported higher rates of abstinence for the high-dose group vs low-dose group, with effects sustained over 24 months.^35^

Supporting the putative impact of ketamine in enhancing effects of psychotherapy more broadly, positive effects of ketamine-assisted cognitive behavioural therapy (CBT) in treatment-resistant depression have also been reported, with CBT sustaining the antidepressant effects of intravenous ketamine (six doses, 0.5 mg/kg, over 3 weeks) over a 17-week period (Quick Inventory of Depressive Symptomatology-Self-Report scores F*=*4.58, p=0.033; d=0.71, 95% CI –0.30 to 1.70).^36^ Furthermore, improvements in cognitive control (eg, executive control, including updating and maintenance) were associated with clinical improvement following ketamine treatment in a subset of patients. This provides some support for the hypothesis that, along with its rapid antidepressant properties, ketamine may also improve cognitive control, while CBT strengthens and maintains these improvements.^36^ A combined approach of ketamine and CBT may therefore have strong potential for MAUD given the neurocognitive impairments and withdrawal-associated dysphoria that appear to hamper psychotherapy effectiveness in this population.

### Objectives

This pilot study aims to determine the safety and feasibility of subcutaneously administered racemic ketamine (three doses, once per week) alongside four sessions of weekly CBT for adults with MAUD, in an outpatient setting. We hypothesise that ketamine-assisted psychotherapy will be safe and feasible in this context.

Secondary objectives are to explore changes from baseline to weeks 5, 8 12 and 24 in methamphetamine use, cravings and withdrawal and quality of life, as well as treatment satisfaction.

Study results will inform future randomised controlled trials.

## Methods and analysis

### Study setting and design

This study is an open-label, single-arm pilot clinical trial. This paper reports on the study protocol in line with Standard Protocol Items Recommendations for Interventional Trials (SPIRIT) guidance (online supplemental file 1).^37^

The study will be conducted in an outpatient stimulant treatment clinic (the ‘Stimulant Treatment Programme’; STP) at St Vincent’s Hospital, Sydney (SVHS), Australia. SVHS, a public teaching hospital, is the study sponsor. Participants will be referred directly from the clinic. Advertising to local health service providers and social media will also be used to enhance recruitment.

### Patient and public involvement

This study is designed and conducted without any involvement from participants or the public. Study results will be disseminated to participants and the public via the National Centre for Clinical Research in Emerging Drugs website.

### Participants and recruitment

#### Eligibility criteria

Eligible participants will be adults who meet DSM-5-TR criteria for MAUD and are seeking treatment to cease or reduce methamphetamine use. Inclusion and exclusion criteria are outlined in table 1.

**Table 1 T1:** Eligibility criteria

Inclusion criteria	Exclusion criteria
All participants must/must be:	All participants must not:
≥18 years of age Able to provide informed consent Willing and able to comply with all study requirements, as determined by the principal investigator Meets DSM-5-TR diagnostic criteria for current stimulant use disorder—amphetamine-type substance—as determined by the principal investigator and confirmed with the MINI Urine drug screen (UDS) point of care (POC) test positive for methamphetamine Willing to register as a client of the St Vincent’s Hospital Sydney (SVHS) Stimulant Treatment Programme (STP)	DSM-5-TR diagnosis of current or past use disorder for ketamine or ketamine analogues as assessed by MINI Prescribed or non-prescribed use of ketamine in the previous 4 weeks Currently enrolled in another treatment trial of MAUD or clinical trial which is likely to affect safety, data quality or may interfere with participation in this study, as determined by the principal investigator Currently pregnant or breastfeeding, or planning on becoming pregnant during the course of the study DSM-5-TR diagnosis of current psychotic disorder as assessed by the principal investigator including review of MINI Current acute suicidality defined as ‘high risk’ using the C-SSRS-6 screener or as determined by the principal investigator DSM-5-TR diagnosis of bipolar disorder as assessed by the principal investigator including review of MINI Current DSM-5-TR diagnosis with other substance use disorders, moderate or severe, except tobacco, caffeine or cannabis as assessed by the principal investigator including review of MINI. Opioid use disorder permitted if stable on opioid agonist treatment; OAT) (ie, no dose changes for 6 weeks if on oral OAT and maximum of one missed dose/week. At least 3 months with no missed doses if on long-acting injectable OAT) History of sensitivity to ketamine or any other components of this product If prescribed antidepressants, the participant must have been on a stable dose for four or more weeks Contraindications to ketamine according to Australian Product Information: Severe cardiovascular disease Heart failure Severe or poorly controlled hypertension Recent myocardial infarction History of stroke Cerebral trauma Intracerebral mass or haemorrhage
Seeking treatment to cease or reduce methamphetamine use If person of childbearing potential, willing to avoid pregnancy for study duration	Any other medical or psychiatric condition which in the opinion of the principal investigator would make participation hazardous. In particular, caution if severe liver, kidney or bladder disease, and also caution if elevated cerebrospinal fluid pressure, increased intraocular pressure, acute intermittent porphyria, seizures, hyperthyroidism, pulmonary or upper respiratory infection, intracranial mass lesions, a presence of head injury, globe injuries, or hydrocephalus Likely or planned surgery, travel, incarceration or other engagement during the study that may interfere with study participation

MAUDmethamphetamine use disorder

#### Participant timeline

Figure 1 gives an overview of the flow of participants through the study. The total study duration for each participant is a maximum of 168 days. This comprises a screening period (window of up to 2 weeks), a 4-week treatment period, end of treatment (week 5), primary endpoint at week 8 and two additional follow-up visits (week 12, week 24).

**Figure 1 F1:**
[figure not shown]
Trial timelines.

Potential participants who express interest in the study will be pre-screened and those who meet basic criteria will proceed to informed consent. Informed consent (online supplemental file 2) will be obtained from each participant by the principal investigator or delegated medical officer. Participants will then be formally screened for eligibility. Screening for eligibility will include medical review and a structured clinical interview (the MINI International Neuropsychiatric Interview 7.0.2; MINI)^38^ for substance use disorders, major depressive disorder, bipolar disorder and psychosis. The Columbia Suicide Severity Rating Scale Screener (CSSRS-6)^39^ will be used to assess for history of suicidal ideation or suicide attempts. Eligible participants will be enrolled in the study. Baseline assessments to characterise the sample include demographic information, the Wender Utah Rating Scale (WURS)^40^ to retrospectively evaluate the presence of childhood ADHD symptoms; and the Substance Use Goals and Expectations to measure treatment goals and expectations (SURGE, unpublished). Qualitative interviews (one per participant) will be conducted during weeks 5 to 8. The full schedule of assessments is outlined in online supplemental file 3.

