Feasibility will be assessed by: (i) time taken to recruit the sample (with a 12-month study timeframe imposed, based on unpublished studies from our group in similar contexts successfully recruiting 20 participants within this timeframe); (ii) proportion of ineligible participants at pre-screening and screening; (iii) number of participants who receive three doses of ketamine, (iv) number of participants who complete four sessions of psychotherapy, (v) retention rate over the full duration of the study, and (vii) acceptability of the intervention, assessed via qualitative interviews. As this is the first study of its kind in this population and pilot studies are not generalisable to other contexts,^57 58^ these will be assessed and reported descriptively. While we conservatively anticipate 50% completion of 4 sessions of CBT and 75% completion of 6-month follow-up assessments based on studies of CBT in this population,^13 59^ these are not directly comparable given the pharmacotherapy component of the present study design. Therefore, results will be synthesised in consideration of the feasibility to progress to larger studies, taking into account the measures described above and, equally so, the qualitative acceptability.^60^

Secondary outcomes include measures of preliminary efficacy and potential mediators. These measures include: (i) self-reported change in the past 28 days of MA use from baseline to week 5 (post treatment), week 8 (primary endpoint), week 12 and week 24 as measured by the TLFB,^56^ (ii) presence of methamphetamine in urine assessed through POC UDS at week 5, week 8, week 12 and week 24, (iii) changes in methamphetamine craving as measured by the Visual Analogue Scale-Craving (VAS-C)^61^ and withdrawal symptoms assessed on the Amphetamine Withdrawal Questionnaire (AWQ)^62^ from baseline to week 5, week 8, week 12 and week 24, (iv) changes in quality of life as measured by the WHO Quality of Life-Brief Version (WHOQOL-BREF)^63^ from baseline to week 5, week 8, week 12 and week 24, and (v) treatment satisfaction as measured by the Treatment Satisfaction Questionnaire for Medication (TSQM-II)^64^ and the Client Satisfaction Questionnaire (CSQ-8)^65^ at week 5 and week 8.

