### Participant retention and withdrawal

The study site will make all reasonable efforts to follow participants for the course of the study. Efforts to minimise loss to follow-up will include respecting participant time commitments, formal tracking procedures including multiple ways to be contacted and strong interpersonal skills of study personnel.

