#### Stopping criteria

If a participant experiences a grade 3 or grade 4 adverse event (AE) considered to be causally related to the study medication, no further study medication will be dispensed until the participant has been reviewed by the site principal investigator.^51^ If the AE is resolved to the satisfaction of the principal investigator, the dose can be recommenced, and the participant will be reviewed the subsequent day. If the AE is not resolved or recurs after recommencing the study medication, the site principal investigator will consider ceasing the medication and withdrawing the participant from the treatment component of the study. Unless they revoke their consent, all participants withdrawn from treatment will continue to be followed as intention to treat.

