### Statistical methods

Descriptive statistics will be used to characterise the study sample. Quantitative analyses will be descriptive and exploratory and include basic measures of central tendency, CIs around means or proportions, Cohen’s d, and paired sample t-tests to assess pre-post intervention changes. P values are considered preliminary and will be reported with caution, supplemented with appropriate metrics (eg, CIs). For categorical measures such as the presence of AEs, rates will be analysed using appropriate non-parametric approaches, such as χ² and relative risk. Quantitative data will be analysed using SPSS Version 29.0.^77^ Qualitative interviews will be collected until all trial participants have been approached. Interviews will be thematically analysed to extract key themes across participant responses, using the approach outlined by Braun & Clarke^78^: familiarising with the data, generating initial codes, searching for themes, reviewing themes, defining and naming themes, and producing the report. Qualitative data will be analysed using NVivo Version 14.^79^

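### Acceptability rests on one interview fixed to weeks 5 to 8, so participants who leave the study before week 5 may go unheard in an outcome that weighs equally in judging progression

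*Protocol article*

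**What the plan says.** The protocol article (Participant timeline, text after Figure 1) fixes the timing: "Qualitative interviews (one per participant) will be conducted during weeks 5 to 8". The Reimbursement section uses the same window and pays $40 for the interview separately, even when it falls on a visit day. Treatment occupies weeks 1 to 4, with ketamine in weeks 2, 3 and 4.

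The Outcomes section lists "acceptability of the intervention, assessed via qualitative interviews" among the feasibility measures, and feasibility is a primary outcome. Progression is to be judged by "taking into account the measures described above and, equally so, the qualitative acceptability". The same section states that "we conservatively anticipate 50% completion of 4 sessions of CBT and 75% completion of 6-month follow-up assessments".

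Three statements bear on whether people who stop early are reached:
- Statistical methods: "Qualitative interviews will be collected until all trial participants have been approached".
- Stopping criteria: "Unless they revoke their consent, all participants withdrawn from treatment will continue to be followed as intention to treat".
- Participant retention and withdrawal: efforts include "formal tracking procedures including multiple ways to be contacted".

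The strengths and limitations box adds that "There is a risk of high attrition rates over the course of the study".

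**The concern.** The reasons people abandon dosing or therapy are among the most useful things a pilot can learn before a randomised trial. The only instrument for acceptability is an interview that cannot take place before week 5. Someone who stops after the first dose in week 2 would be interviewed three to six weeks later (5 − 2 = 3; 8 − 2 = 6), if still reachable and willing. The two satisfaction scales, which are secondary outcomes, are also collected only at weeks 5 and 8. Nothing in the text shown that measures acceptability or satisfaction is therefore timed to when a participant leaves.

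If those who are missed hold less favourable views, the themes from the interviews obtained would be more positive than those of the whole sample. That picture would enter the progression judgement with the same weight as the quantitative measures. Views not collected at exit cannot be recovered later.

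**Working it through.** The plan states no expected number of interviews, no acceptability percentage and no threshold, so there is no figure to reproduce. Two checks are possible.

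**1. What the plan's own expectations imply.** Inputs: 20 participants (Sample size); 50% completing four therapy sessions and 75% completing the 6-month assessments (Outcomes).
- Therapy completers: 0.50 × 20 = 10; non-completers: 20 − 10 = 10.
- Seen at week 24: 0.75 × 20 = 15; not seen: 20 − 15 = 5.
- Fewest non-completers seen at week 24, which is the case where all 10 completers are seen: 15 − 10 = 5.

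The plan thus expects at least 5 of the 10 non-completers to be in follow-up well after the interview window. Assuming anyone seen at week 24 could also be reached in weeks 5 to 8, at most about 5 participants would be out of reach during the window. The Outcomes section itself cautions that the two percentages come from studies not directly comparable with this one, so they are a guide only.

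**2. How selective non-response would act.** This is an illustration, because the plan analyses interviews by theme and estimates no proportion. Let *a* and *b* be the proportions of completers and non-completers who find the intervention acceptable. Let *m* be the number of the 10 non-completers interviewed, and suppose all 10 completers are interviewed. Then

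bias = (10a + mb)/(10 + m) − (10a + 10b)/20.

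The values of *a* and *b* are assumptions; none is in the document.

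| a | b | true value | m = 0 | m = 5 | m = 10 |
|---|---|---|---|---|---|
| 90% | 50% | 70% | 90% (+20) | 76.7% (+6.7) | 70% (0) |
| 90% | 30% | 60% | 90% (+30) | 70% (+10) | 60% (0) |
| 80% | 60% | 70% | 80% (+10) | 73.3% (+3.3) | 70% (0) |
| 70% | 70% | 70% | 70% (0) | 70% (0) | 70% (0) |

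Worked example, first row with m = 5: (10 × 0.9 + 5 × 0.5)/15 = 11.5/15 = 76.7%, against (9 + 5)/20 = 70%.

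Two things follow. The bias is zero if non-completers are all interviewed, or if they hold the same views as completers, so both selective absence and a difference in view are needed. The m = 0 column, where every non-completer is missing, is not what the plan's figures imply. The m = 5 column is closer to them, and there the shift is 3.3 to 10 points when views differ as assumed.

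**The case against.** A reader might infer that everyone who stops early has gone by week 5 and that the acceptability result is therefore biased upward. The document does not support that. Stopping treatment is not leaving the study: withdrawn participants are followed unless they revoke consent, every participant is to be approached for interview, tracking uses several contact routes, and the interview carries its own payment. The plan also expects 75% follow-up at 6 months against 50% therapy completion, which makes sense only if many non-completers stay in contact.

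Four further arguments deserve weight.
- Acceptability is analysed thematically, so a few dissenting interviews can supply the negative themes, and a bias in a proportion does not carry over directly. This stands, and it is why the table above is only an illustration.
- Early stopping also shows in the counts of doses received and therapy sessions completed, and in retention. This stands too, but those counts show that people stopped, not why.
- A post-treatment interview covering the whole course is a defensible choice. It is, for those who finish or stay in contact, and the default window should be kept for them.
- An exit interview may be described in the full protocol or in the supplementary schedule of assessments, neither of which is shown. That is possible. However, the window is a stated choice, given in two sections of the article, rather than a detail left out. If an exception exists, the wording should acknowledge it.

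The safeguards reduce the risk without removing it. Being approached is not being interviewed, and continued follow-up does not cover those who revoke consent or stop attending.

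**Conclusion.** The point holds as a risk of selective non-response. As written, the plan gives no opportunity to interview a participant who revokes consent or is lost before week 5, and it reaches others who stop early only some weeks afterwards, when they may decline. Whether this makes acceptability look better than it is depends on two unknowns: how many are missed, and whether they think less well of the intervention. The document gives neither, so the size cannot be derived. The plan's own expectations suggest that about 5 of 20 participants at most would be out of reach, on the assumption that those seen at week 24 are also reachable in weeks 5 to 8; refusals would come on top of that. The claim that acceptability *is* biased upward goes beyond the text. The sample size is unaffected. The change is still worth making, because the measure counts equally towards progression and the change costs little.

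**What to change.** Keep weeks 5 to 8 as the default. Add that the same single interview will be offered early, by telephone if preferred, to any participant who withdraws consent or says they will not continue attending. It should be made at the time they say so, and only with their agreement. Align the Reimbursement wording so that the same $40 covers an interview held outside the window.

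Report the numbers approached and interviewed by ketamine doses received and by therapy sessions completed. Present the themes for completers and non-completers before any statement on progression.

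The cost is a change of protocol wording and some scheduling flexibility: still one interview and one payment per participant. The downsides are small. The interval between last dose and interview will vary more, so the timing of each interview should be recorded. Participants lost without notice will still be missed, which is a further reason to report the counts.
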